#### Mechanical muscle strength

Isometric muscle strength (iMVC) for knee extensors, hip extensors, hip flexors and hip abductors using stabilized dynamometry.

#### Physical performance battery

Physical performance-based measures will include: 30-second repeated chair raise test (number completed), 20-meter fast-paced walk (time in seconds), 30-second single-leg knee bending (number completed), and Timed Up and Go (time in seconds).

#### General health status (EQ-5D-5L)

A utility index for use in health economics. It is based on a descriptive system that defines health in terms of five dimensions: Mobility, Self-Care, Usual Activities, Pain/Discomfort, and Anxiety/Depression [38].

#### Cost-effectiveness

This will be estimated as the ratio between the cost of the intervention and the effect it produces. The total cost will be estimated from register-based costing of primary care, secondary care (length of hospital stay, re-admission, visits at the emergency room and out-patient clinic) and patient’s out-of-pocket costs (transportation expenses and time spent on transportation and receiving health care). Quality of Life Adjusted Years (QALYs) will be used for the analysis and calculated using changes in EQ-5D-5L from baseline to the 12-month follow-up. Patient-reported values are weighted using Danish tariffs [39].

#### Poor compliance

Poor compliance is not uncommon in studies of non-surgical treatments [40]. Achieved exercise dose and reasons for poor-compliance will be recorded.

#### Joint-specific adverse events

Joint-specific adverse events will be determined as: 1) not attending a training session and/or ceasing training because of increased pain/problems in the index joint related to the training; and 2) self-reported pain level > 5 on the VAS scale after training. The reasons for not attending a session due to pain/problems related to training or to other factors will be recorded.

### Sample size

One year has been selected as a clinically relevant period to postpone surgery. The survival probability in the education plus exercise group at one year is estimated to be 0.80 and 0.60 for the education only group. Survival group differences will be tested using log-rank statistics. To achieve a statistical power of 80% (β=0.20), the estimated sample size for a two-sample comparison (days without surgery) of survivor functions (log-rank), a sample size of n=86 is needed in each group to detect statistically significant differences (for α=0.05). Allowing for no more than 15% drop-out, 200 patients in total will be recruited.

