## Methods and materials

### Study design

A prospective, blinded, parallel-group, multi–center trial (2 sites), with balanced randomization [1:1], in accordance with CONSORT (Consolidated Standards of Reporting Trials) guidelines [20].

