### Participants and recruitment procedures

Patients aged 40 years and older with an indication for total hip replacement (THR) for hip OA will be consecutively recruited from the outpatient clinic at the Department of Orthopedic Surgery and Traumatology, Odense University Hospital, and Vejle Hospital, Denmark. The inclusion and exclusion criteria are listed in Table 1. The indication for THR will be based upon symptoms, a clinical examination and radiographic findings [21]. Although, defining the cut points for symptoms and functional disability which indicate the need for a hip replacement is complex [22]. Data on multiple other factors such as home situation, co-morbidities, and marital status will be collected at baseline. An independent radiologist will assess the stage of hip OA severity using the Kellgren-Lawrence grading scale [23].

**Table 1 T1:** Criteria for participants in the study

**Inclusion criteria**	**Exclusion criteria**
40 years and older	Inflammatory joint disease
Indication for total hip replacement	Earlier ipsilateral proximal femur fracture
Residency within local municipality or willing to commute	Hip pain < 3 months
	Neuropathy or neuromuscular disease
	Malignant disease
	Diseases where a moderate level of physical exercise is contraindicated
	Inability to speak or read Danish
	Inability to participate for other reasons
	Refusal to participate

On initial contact, patients will be examined and an indication for hip surgery will be assessed by an orthopedic surgeon. Where all inclusion criteria and none of the exclusion criteria are met, the patients will be invited to participate and will receive verbal and written information about the trial (background, procedure, randomization, and potential risks). In addition, a standardized information video without technical or value-laden terms will be provided to patients to ensure impartiality between treatments and consistency at both hospitals. Information will be given in an undisturbed location within the outpatient clinic, and time will be made available for questions. Subsequently, the patients will receive the written consent form. Patients wishing to have some reflection time will be given a stamped addressed envelope, and contacted by the research nurse no later than 2 days after consultation. Patients who choose not to have reflection time will sign the written consent form, be randomized, and scheduled for the completion of baseline measurements.

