### Primary outcome measure

Cumulative Survival analysis (Kaplan-Meier survival curve).

Cumulative survival is measured as the time in days without total hip replacement surgery since inclusion.

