### Statistical analysis

All outcome measures will be checked for Gaussian distribution, and non-parametric data will be analyzed using a Mann–Whitney rank sum test [41]. The treatment effect will be analyzed using a random effects mixed linear model (repeated measures) [42]. Hence, correlated measurements from the same patient can be modeled. Model assumptions are checked by residual plots and the model includes the interaction between treatment and elapsed time, adjusted for baseline values. All analysis will follow the intention-to-treat principle [43]. However, subsequent analysis using last observation carried forward may be required. Finally, the number needed to treat (NNT) for a positive effect of treatment (no surgery after 1 year) will be analyzed. All statistical analyses are blinded and will be performed using Stata 11 software (StataCorp, TX, USA).

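### The primary log-rank test uses no baseline information; a pre-specified Cox model stratified by hospital and adjusted for baseline severity may gain power, by an amount the protocol cannot establish

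*Protocol article*

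**What the plan says.** The single primary outcome is time to surgery (Primary outcome measure): "Cumulative survival is measured as the time in days without total hip replacement surgery since inclusion". The only test named for it is in Sample size: "Survival group differences will be tested using log-rank statistics". No covariate or stratum is mentioned there.

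Baseline adjustment appears once, in Statistical analysis, for the repeated-measures linear mixed model: "the model includes the interaction between treatment and elapsed time, adjusted for baseline values". That model serves repeated scores, not time to surgery.

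Three candidate variables are already available:

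- Hospital, the only stratification factor (Randomization and allocation concealment).
- Radiographic grade (Participants and recruitment procedures): "An independent radiologist will assess the stage of hip OA severity using the Kellgren-Lawrence grading scale". No time point is given, but it is described together with the baseline data.
- HOOS, completed by patients at baseline and at each follow-up (Discussion).

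Participants and recruitment procedures also says that the indication for surgery rests on symptoms, clinical examination and radiographs.

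**The concern.** The repeated scores get baseline adjustment and the one primary outcome does not. Symptoms and radiographic findings contribute to the indication for surgery, so HOOS pain and Kellgren-Lawrence grade may also predict who is operated on within the year.

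If they do, two things follow for a time-to-event comparison. Leaving out a strong prognostic factor pulls the hazard ratio towards 1. Chance imbalance in severity between the arms also goes uncorrected, because the randomization balances only hospital. With about 52 events expected, a pre-specified adjustment could buy power without recruiting anyone.

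**Working it through.** **1. Reproduce the plan's figure.** Inputs from Sample size: the one-year surgery-free probability with exercise "is estimated to be 0.80 and 0.60 for the education only group", power 80%, α 0.05. Allocation is 1:1 (Study design). Sidedness is not stated; two-sided is assumed.

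- Implied hazard ratio: ln 0.80 / ln 0.60 = 0.437.
- Freedman events: (1.960 + 0.842)² × [(1 + 0.437)/(1 − 0.437)]² = 51.09.
- Per group: 51.09 / (0.20 + 0.40) = 85.15, rounded up to **86**, as stated.

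So the sample size was built for a log-rank test without covariates, and it is right for that test.

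**2. Power as planned.**

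- 172 patients: 172 × 0.30 = 51.6 events. Power is 80.4% (Freedman) or 84.5% (Schoenfeld).
- 200 recruited with 15% lost: 170 patients, 51 events. Power is 79.9% (Freedman) or 84.1% (Schoenfeld).

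Power is at or about the target without adjustment.

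**3. What adjustment could add.** The document does not say how strongly grade or HOOS predicts time to surgery. Prognostic strength is therefore an assumption, varied as the hazard ratio per SD of one normally distributed baseline score.

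In every setting the arm hazards were solved so that marginal one-year survival stays at 0.80 and 0.60. Event times are exponential given the score, censoring is at one year, and there are 86 patients per arm. Tests reject at 1.96. Run A has 2,500 trials per setting (unadjusted v adjusted Cox). Run B has 4,000 (log-rank v adjusted Cox).

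| HR per SD (assumed) | Run A, unadjusted / adjusted | Gain | Run B, log-rank / adjusted | Gain |
|---|---|---|---|---|
| 1.0 | 82.3% / 82.2% | −0.1 | 83.7% / 83.1% | −0.6 |
| 1.35 | 83.0% / 84.2% | +1.2 | 83.0% / 83.7% | +0.7 |
| 1.65 | 82.4% / 85.2% | +2.8 | 83.8% / 86.5% | +2.7 |
| 2.0 | 81.2% / 87.4% | +6.2 | 82.9% / 88.0% | +5.1 |
| 2.7 | 82.2% / 93.3% | +11.1 | 83.5% / 92.8% | +9.3 |

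The simulation standard error of one power figure in run B is about √(0.83 × 0.17 / 4000) = 0.6 points. A third run of 1,500 trials per setting gave 81/81, 82/83, 84/87, 83/89 and 82/93%. With no treatment effect, type I error was near 5% for both analyses.

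**4. Reading.** Unadjusted power stays at 81% to 84% throughout, so the planned test does not fall below its target. What varies is how much more the adjusted test would have. Because marginal survival is held fixed, the gain is in the test itself and not merely a hazard ratio further from 1.

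**The case against.** **Nothing is wrong in the plan.** The test is valid under randomization, agrees with the sample size and reaches the stated power. The article is condensed, and an analysis plan that is not shown may contain an adjusted survival model. All of this stands, and it keeps the point at the level of a suggestion.

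**The tempting stronger reading.** A reader might infer that the unadjusted test throws power away, or that the trial is underpowered without adjustment. The document supports neither. It gives no prognostic strength. An indication for surgery is an inclusion criterion, so every participant already has one and the spread of severity may be narrow. The link from symptoms and radiographs to the indication does not show that they predict when an already indicated patient is operated on. If they predict it weakly, the gain is at most about one point.

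**Simulation limits.** It uses one continuous score with a log-linear effect, whereas the proposal combines HOOS pain, an ordinal grade and hospital strata. The upper gains need not carry over.

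**Baseline timing.** Randomization and allocation concealment has envelopes opened only after all baseline assessments. Participants and recruitment procedures has patients who waive reflection time randomized first and then scheduled for baseline. HOOS is self-reported by patients who cannot be blinded, so a value given after allocation is known could bias an adjusted analysis. This objection stands and is a condition of the fix.

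**Different estimand.** An adjusted hazard ratio is conditional on the covariates, while the design contrast of 0.80 against 0.60 is marginal. This also stands; reporting one-year survival by arm keeps the marginal contrast in view.

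**Conclusion.** The point holds as an optional improvement in efficiency. The only test named for the primary outcome ignores the stratification factor and two severity measures that are already collected. The log-rank test is nevertheless valid and delivers about the 80% power it was sized for.

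At 86 per arm, adjustment may add about 0 to 1 point if the covariates are weak (hazard ratio per SD up to 1.35), about 3 points at 1.65, 5 to 6 at 2.0 and 9 to 11 at 2.7. Where this trial lies in that range cannot be established from the document. The figures assume the plan's own 0.80 and 0.60, a two-sided 5% test, one year of follow-up and a single normal score. Since nothing material is lost when the covariates are useless, the change is worth making, provided HOOS was recorded before allocation was known.

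**What to change.** Before unblinding, amend the analysis text as follows:

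- **Primary test and estimate:** a Cox model for days to hip replacement over the first year, stratified by hospital and adjusted for baseline HOOS pain (continuous) and Kellgren-Lawrence grade, with the coding of grade fixed in advance.
- **Supporting:** the Kaplan-Meier curves with one-year survival by arm, and the log-rank test.
- **Sample size:** leave as stated.
- **Baseline timing:** reconcile Participants and recruitment procedures with Randomization and allocation concealment, so that baseline HOOS is recorded before allocation is known. Use only HOOS values recorded before the envelope was opened and treat later ones as missing.
- **Missing baseline values:** name one simple imputation rule in advance.

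The cost is a few lines of wording, a check of HOOS completion dates against envelope-opening dates, and an imputation rule. No new data collection or recruitment is needed. The downside is that the reported hazard ratio is conditional on the covariates.

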### Statistical analysis

All outcome measures will be checked for Gaussian distribution, and non-parametric data will be analyzed using a Mann–Whitney rank sum test [41]. The treatment effect will be analyzed using a random effects mixed linear model (repeated measures) [42]. Hence, correlated measurements from the same patient can be modeled. Model assumptions are checked by residual plots and the model includes the interaction between treatment and elapsed time, adjusted for baseline values. All analysis will follow the intention-to-treat principle [43]. However, subsequent analysis using last observation carried forward may be required. Finally, the number needed to treat (NNT) for a positive effect of treatment (no surgery after 1 year) will be analyzed. All statistical analyses are blinded and will be performed using Stata 11 software (StataCorp, TX, USA).

### Facilities, organization and timeline

Exercise professionals from the local municipal health agency will participate. The project utilizes already established exercise facilities within the municipality. This collaboration between several health care professionals enables us to conduct a clinically founded randomized trial based on evidence from several research areas. The use of a multi-center design facilitates recruitment, and possible implementation of a new treatment strategy. Inclusion of patients will commence 2013 and end 2014 and with the 12 month follow-up, the last patient will be followed-up in 2015. In the continuation of this trial, we intend to follow patients (prospective observational cohort study) to provide long-term results (Figure 1).

### Ethics

The trial complies with the Declaration of Helsinki and ethics approval has been granted by the Regional Ethics Committee of Southern Denmark, approval number S-20120109. The trial is registered with ClinicalTrials [44] (NCT01697241).

## Discussion

To our knowledge this is the first randomized clinical trial comparing the effect of a patient education plus supervised exercise program to education alone on the time to total hip replacement in patients with an indication for hip replacement surgery.

Such a trial is warranted because exercise as non-surgical treatment may help to postpone or eliminate the need for TJR without deterioration and also improve health-related quality of life through enhanced function and decreased pain. Hence, studying patients with this severe disease condition is clinically important. Further, the primary outcome measure ‘time in days without surgery’ was chosen because TJR should only be recommended once improvements cannot be achieved by other treatment strategies. Moreover, postponing or avoiding TJR is the most relevant outcome when it comes to: reducing health care costs providing the program is cost-effective, minimizing complications, and improving healthcare pathways. Finally, such a trial is also warranted because the recommendations for lower extremity exercises are based on studies of knee OA patients. Although exercise trials on patients with hip OA have been conducted, most of these studies have also included patients with coexisting knee OA, and results were not joint-specifically reported, or too few patients with hip OA were included, preventing valid conclusions to be drawn [6,9,12,15]. Consequently, evidence supporting exercise for patients with hip OA is needed [14].

The secondary outcome measures used in this trial are those recommended for use in clinical studies of OA, and include patient-reported outcome measures (PROs) for pain, physical function, physical activity, health-related quality of life, and global response to treatment [36]. The patients will be asked to rate their current hip condition at baseline, and at each follow up (HOOS questionnaire), but also to rate possible change in their condition since baseline (GPE questionnaire). The 3-month follow-up was chosen to identify possible improvements at the end of the intervention period. Three months is also a reasonably long timeframe for clinical improvements to occur in patients with long-standing hip pain, yet short enough to assume that patients would be able to recall their baseline condition. The 12-month follow-up was chosen to match the clinically relevant period for postponing hip replacement surgery.

As for the other measures, both muscle mechanical and physical performance-based outcome measures will be part of the evaluation for primarily three reasons. First, muscle mechanic outcomes provide information about the effectiveness of the exercise intervention in terms of improving muscle strength, and both muscle weakness [45] and muscle asymmetry [46,47] have been found to be present in hip OA patients. Second, physical performance-based outcomes provide information about the effectiveness of the exercise intervention in terms of improved function in tasks resembling daily activities. Third, muscle atrophy has been associated with functional limitations in aging individuals [48], and this trial is adequately powered to further explore such associations. Furthermore, measures of exercise-related pain, adherence, and joint-specific adverse events are essential for evaluating the feasibility of the exercise intervention program. Finally, the cost-effectiveness of non-surgical interventions for hip OA is needed [49]. Total costs during the first year will be compared with gains on the HOOS and the patient’s perceived effect (GPE), and the societal costs of the intervention per patient during the first year and the incremental qualify of life in years/days, as obtained from the EuroQol (QALY during the first year). The gain in health and the costs associated with the heath gain could possibly be used as a decision-making aid for optimal resource allocation.

A number of considerations went into designing the supervised exercise intervention in this trial. One consideration was how to prescribe an exercise program, where the level of progression gradually increases, without provoking persistent pain. The use of self-reported pain (VAS) immediately after each exercise session has previously proven to be a feasible way of adjusting the level of progression [18]. Hence, patients who experience recurrent high risk pain after exercise or whose pain either doesn’t return to ‘pain as usual’ or increases during the day following exercise will be asked to reduce the level of exercise to the previous level of progression.

Another consideration was selecting the type of exercises to be used in this trial. An exercise program based on neuromuscular principles has been shown to be patient- and goal-oriented and feasible for elderly patients scheduled for hip and knee replacement [18]. All exercises are individualized with progression guided by the patient’s neuromuscular function, and for each exercise, three levels of progression are available, meaning the program can be tailored to the individual’s pain level and function. It utilizes functional exercises and emphasizes neutral alignment of the hip, knee and foot to resemble conditions in daily life and more strenuous activities, without compromising the quality of the performance. Another exercise program using progressive high load (intensive) resistance training principles has been shown to be effective in elderly patients in the early postoperative phase [19] and elderly hospitalized patients [50]. Also, evidence of the efficacy of general pre-operative strengthening exercises exists [4], and strengthening exercises alone show moderate effect on pain and function in patients with OA [51]. Rather than using general strengthening exercises, the use of high load (70-80% of 1RM) in the current trial is based on evidence from systematic reviews, where the intensity of the training was the strongest factor affecting strength and functional outcome [16,17]. To be effective, exercises must target isolated muscle groups, be progressive [26,27], and possibly be combined with a more complete exercise program [51]. Both exercise programs in this trial are supervised, based on individualized goal-based patient treatment that allows the program to target the presenting musculoskeletal impairments that contribute to the patient’s symptoms and functional limitations. This approach aligns with the guidelines from EULAR, which recommend tailored treatment [14].

A final consideration was how to most effectively distribute the two types of exercises throughout the intervention period, and across each week. We decided to mimic performance enhancement in sports. As a result, neuromuscular and intensive resistance exercise sessions will be administered on separate days within the same week, so that separate session goals can then be pursued.

Optimal outcomes in population health require both efficacious treatments and adherence to those treatments. Adherence to health interventions is a complex issue, especially for individuals with chronic conditions [52]. The interaction between patients and providers in terms of verbal communication, physical interaction and empathy could affect the patient’s enthusiasm, adherence, and participation. Nevertheless, it can be enhanced by the use of supervised, class-format exercise sessions in the initial exercise period [10] combined with later ‘refresher or booster’ sessions [52,53]. Also, to minimize the provider effect, three physiotherapists will randomly interact and execute the training program at each center in this trial.

The internal validity of the trial may be affected by a negative performance bias in the group who receive patient education only, as they may feel neglected and missing out on active treatment. The exclusion criteria always limit the generalizability to other populations. For example, the results from this trial may not be generalized to an individual patient with hip OA who is not fit enough to take part in moderate-to-high intensity exercise. Conversely, the external validity is improved by the multi-center design, and the delivery of the interventions by multiple practicing community physiotherapists. Also, the intervention will be implemented for both genders, a wide age range, and in patients with severe hip OA. Hence, it is reasonable to assume that the program could benefit the general hip OA population. Lack of adherence is a potential confounding factor for the outcomes in this trial. Consequently, the number of sessions completed will be recorded, and patients will be asked specifically at follow-up points if they have initiated other treatments for their hip condition since the last examination [52].

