**Methods/design:**

A prospective, blinded, parallel-group multi-center trial (2 sites), with balanced randomization [1:1]. Patients with hip osteoarthritis and an indication for hip replacement surgery, aged 40 years and above, will be consecutively recruited and randomized into two treatment groups. The active treatment group will receive 3 months of supervised exercise consisting of 12 sessions of individualized, goal-based neuromuscular training, and 12 sessions of intensive resistance training plus patient education (3 sessions). The control group will receive only patient education (3 sessions). The primary end-point for assessing the effectiveness of the intervention is 12 months after baseline. However, follow-ups will also be performed once a year for at least 5 years. The *primary* outcome measure is the time to hip replacement surgery measured on a Kaplain-Meier survival curve from time of inclusion. *Secondary* outcome measures are the five subscales of the Hip disability and Osteoarthritis Outcome Score, physical activity level (UCLA activity score), and patient’s global perceived effect. *Other* measures include pain after exercise, joint-specific adverse events, exercise adherence, general health status (EQ-5D-5L), mechanical muscle strength and performance in physical tests. A cost-effectiveness analysis will also be performed.

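### The one-year economic horizon matches the hypothesised delay in surgery, so it cannot separate deferred from avoided hip replacements

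*Protocol article*

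**What the plan says.** The horizon is stated in two places, and both give one year.

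- **Other measures, Cost-effectiveness.** QALYs are "calculated using changes in EQ-5D-5L from baseline to the 12-month follow-up". On the cost side, "The total cost will be estimated from register-based costing of primary care, secondary care" and patients' out-of-pocket costs. Hospital stay is part of secondary care, so a replacement inside the window is charged.
- **Discussion.** "Total costs during the first year will be compared with gains on the HOOS" and with the global perceived effect. The section also names "the societal costs of the intervention per patient during the first year", set against quality-of-life gain "as obtained from the EuroQol (QALY during the first year". It adds that the result might serve as an aid to allocating resources.

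The aim under Specific objective and hypothesis is postponement of surgery. Sample size says: "One year has been selected as a clinically relevant period to postpone surgery". The Discussion states that the 12-month visit was chosen to match that period, and it distinguishes postponing the need for surgery from eliminating it.

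The Abstract says that "follow-ups will also be performed once a year for at least 5 years". Facilities, organization and timeline describes this continuation as an observational cohort. Neither section links it to the economic analysis.

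**The concern.** A one-year within-trial evaluation is common and often harmless. Here the cut-off falls on the quantity under test. Every participant has an indication for hip replacement at entry, and the hypothesis is that exercise delays the operation. A patient operated on at day 360 brings the cost of surgery into the analysis. A patient operated on at day 380 brings none, exactly like a patient who is never operated on.

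Deferral is a realistic possibility on the plan's own facts: supervised exercise lasts 12 weeks, after which patients are only encouraged to continue on their own.

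The QALY side is cut at the same point. Any benefit of a first-year operation that comes after month 12 is not counted, and the plan expects twice as many first-year operations in the control arm (40% vs 20%).

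At stake is what the economic result can be taken to mean. The Discussion gives "reducing health care costs providing the program is cost-effective" as one reason why postponement is the most relevant outcome, and the Conclusion promises evidence on cost-effectiveness. A reader who takes a one-year saving as a lasting one could be badly wrong, and the stated analysis gives no means of knowing.

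**Working it through.** **Inputs from Sample size:** surgery-free probability at one year 0.80 (education plus exercise) and 0.60 (education only); power 80%; α = 0.05 (two-sided assumed); 86 per group.

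**The plan's own figure.** Hazard ratio = ln 0.80 / ln 0.60 = 0.437. Freedman's log-rank formula gives (1.960 + 0.842)² × [(1 + 0.437)/(1 − 0.437)]² ≈ 51.1 events. The mean one-year event probability is (0.20 + 0.40)/2 = 0.30, so the total is 51.1/0.30 ≈ 170.3, or 85.2 per group, rounded up to 86. The stated sample size is reproduced and is not in dispute. The same two probabilities are used below.

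**What the one-year analysis credits.** Operations in year one per 100 patients are 20 vs 40, a gap of 20 in favour of exercise. The article gives no unit costs, so size is shown in operations, not money.

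**What happens to the gap after year one.** The documents give no later surgery rates, so each scenario is an assumption.

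1. *Both arms share the control hazard after year one* (control risk stays at 40% a year). Gap at year t = (0.80 − 0.60) × 0.60^(t−1).
2. *The hazard ratio of 0.437 persists with constant hazards.* Gap at year t = 0.80^t − 0.60^t.

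| Year | Shared control hazard, per 100 | HR 0.437 persists, per 100 |
|---|---|---|
| 1 | 20 | 20 |
| 2 | 12 | 28 |
| 3 | 7.2 | 29.6 |
| 5 | 2.6 | 25 |
| 7 | 0.9 | 18.2 |

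Under scenario 1 the one-year figure overstates the difference in operations by 20/12 = 1.7-fold at year 2 and 7.7-fold at year 5. Under scenario 2 it understates the difference until about year 7. These gaps are undiscounted.

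3. *All 20 operations are only deferred.* The undiscounted saving is 0. With discount rate r and deferral of d years, the share of the credited saving that is real is 1 − 1/(1 + r)^d. This is 2.9% for r = 3%, d = 1 and 17.7% for r = 5%, d = 4. Both the rates and the delays are assumed.
4. *A fraction f is deferred and the rest avoided.* The undiscounted gap is 20(1 − f): 15, 10 and 5 for f = 0.25, 0.50 and 0.75.

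**Where the direction turns.** With control risk at 40% in year two, the gap stays at 20 if 0.80 × q = 0.60 × 0.40, so q = 0.30. The year-two hazard ratio is then ln 0.70 / ln 0.60 ≈ 0.70. Above that value the one-year figure overstates the two-year gap; below it, the figure understates it.

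**The case against.** A reader might infer that the analysis is biased towards exercise, or that a successful trial yields a favourable economic result by construction. The documents do not support that. The direction depends on surgery rates after month 12, which are not given, and under a persistent effect the one-year gap is too small. Other truncations work against exercise: the 24 supervised sessions fall wholly inside year one, while any later benefit falls outside it. Health gains by month 12 in controls who have been operated on count for control. The ratio also depends on programme cost, surgery cost and QALYs, so success on the primary outcome does not settle it. All of this stands.

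A reader might also infer that almost the whole credited saving, about 97% at 3% discounting, is an artefact. That needs the entire gap to close in year two. With control risk at 40% a year, 64% of controls are operated on by then. The exercise arm would have to go from 20% to 64%, a year-two risk of 44/80 = 55% among those not yet operated on. That is a hazard ln 0.45 / ln 0.60 ≈ 1.56 times control. It is an extreme case, not a central estimate.

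Nor is the objective unanswerable: a 12-month evaluation can be carried out as described. The article names the first year openly, claims no saving beyond it, speaks only of a possible decision aid, and lists cost-effectiveness outside the primary and secondary outcomes. Scenario detail may be left to a fuller document, and the content of the yearly questionnaires is not described.

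The core remains. The article itself fixes the horizon, the horizon equals the hypothesised delay, and the later follow-up that could separate deferral from avoidance is not tied to the economics.

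**Conclusion.** The concern holds in conditional form. The economic analysis can estimate first-year cost-effectiveness, but it cannot say whether a first-year difference in operations is a saving or a delay. It overstates the saving to the extent that surgery is only deferred past month 12, and may understate it if the effect lasts. From the planned gap of 20 per 100, the assumed scenarios run from 2.6 (shared control hazard) to 25 (persistent HR 0.437) at year 5, and to zero before discounting under full deferral. The planning probabilities are the protocol's; everything after month 12 is assumption. The truncation of QALYs probably adds in the same direction for deferred cases, but it cannot be sized because the article gives no timing of surgery and no utilities.

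This is a worthwhile and inexpensive improvement to the economic analysis. It does not touch the primary outcome or the sample size.

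**What to change.** 1. In Cost-effectiveness and in the economic paragraph of the Discussion, present the result as a 12-month within-trial estimate, and state that no conclusion on lasting savings will be drawn from it.
2. Add scenario analyses for operations after month 12, with discounting, covering at least full deferral, equal hazards and a persistent effect, so that both directions are shown.
3. Extend the register-based costing by randomised group over the yearly follow-up of at least 5 years. Include EQ-5D-5L in that follow-up if it is not already collected, and base any longer-term economic conclusion on these data.

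The cost is protocol wording, a little more analysis, and one later register extract with a short questionnaire in a follow-up already planned. The price is also a later definitive economic result, whose direction is not known in advance.
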